### Analysis

Analyses will be conducted and reported according to the Consolidated Standards of Reporting Trials (CONSORT) statement [87]. The results will be disseminated in peer-reviewed scientific journals. The depersonalized data will be analyzed based on the intention-to-treat principle. Missing data will be handled using multiple imputations with 10 estimations per missing value following recommendations of Little and Rubin [88] and Schafer [89]. Differences in continuous outcomes between the groups will be analyzed using analysis of covariance (ANCOVA), with pre-scores as a covariate and the post-scores as the dependent variable. Possible confounders (e.g. former use of psychotherapy) will be assessed and included as covariates if they should be associated with changes in the primary outcome. We will compute standardized effect sizes (Cohen’s d including the 95% confidence intervals for all effect sizes). We will also test differences in treatment response rates (50% relative symptom reduction), numbers of participants displaying reliable change (according to Jacobson and Truax [90]) as well as differences in symptom deterioration rates. Effect sizes between groups of dichotomous outcome variables will be expressed as number needed to treat and its associated 95% confidence intervals. All reported *p*-values are (one-sided) at a significance level of 0.025 for the primary outcomes and 0.05 for the secondary outcomes.

Moderators of the outcome will be analyzed on an exploratory basis using regression analyses, as well as region of significance procedures [91], in case of significant findings. Baseline variables considered for moderator analyses include: Sociodemographic and study-related characteristics (e.g. age, gender, nationality, full-time versus part-time students, study major, number of semesters on leave, number of semesters in total, ECTS points), baseline severity of social phobia (SIAS, SPS), depressive (BDI-II) and general psychopathological symptoms (BSI), interpersonal problems (IIP), fear of positive evaluations (FPE), health-related quality of life (AQoL), generalized vs. specific SAD, concurrent use of psychotropic drugs, prior mental health treatment, perceived treatment credibility (CEQ), comorbid depressive disorders (SCID), number of comorbid disorders (SCID), age of onset (SCID). Moderator analyses will not be adjusted for multiple testing, as the aim is to generate hypotheses to be tested in future confirmative studies. All directional hypotheses are tested one-sided, bidirectional hypotheses two sided.

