One of the major cost-drivers and potential barriers for large-scale treatment dissemination is the provided level of therapeutic guidance in IMIs. In a recent meta-analysis guided IMIs yielded a mean average effect of g = 0.87 [0.72–1.02] compared to passive control conditions such as WLC (*n* = 11) [25]. The standardized effect size of unguided IMIs was g = 0.78 [0.50–1.05] compared to passive controls (*n* = 8). The effect sizes (0.28–1.47) varied widely between unguided IMIs [27–34], which makes it difficult to anticipate the expected effect size for future studies. We suspect that the variance in effect sizes between studies could be explained by methodological differences such as small (*n* = 20–40) [27, 29–32] to moderate (*n* = 56–62) [28, 34] sample sizes, different lengths of follow-ups (e.g. only three studies evaluated long-term effects [27–29]) and high dropout rates. Therefore, additional research is needed to determine the efficacy of unguided internet-based interventions in the treatment of SAD, particularly among university students.

Although it is often assumed that IMIs tend to be cost-effective, there is limited empirical evidence showing the impact on health economic outcomes [35–37]. To the best of our knowledge, only three studies investigated the cost-effectiveness of IMIs for SAD; all of these studies evaluated a therapist guided IMI [38–40]. To date, no study has investigated the cost-effectiveness of an internet-based intervention in university students, and no study has evaluated the health economic effects of an unguided internet-based intervention for SAD.

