### Randomization

Two hundred participants will be randomly assigned. The allocation list is produced by a random number generator Randlist [9] which randomly allocates participants in a 1:1 ratio with a block size of 8 to either IMI or WLC. The list is operated by an independent researcher not otherwise involved in the study. This researcher has no information about the participants other than the participants’s trial ID numbers and will randomize the participants in the order of the incoming informed consent form. During the randomization process, the allocation will be concealed from participants and researchers involved in recruitment. Participants will not be blinded to study conditions.

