### Power and sample size calculation

The study is powered to detect small to medium effect sizes of d = 0.4. The intended sample size of 200 participants will provide sufficient power to detect a significant standardized effect size (Cohen’s d) of 0.4 on the primary outcome variable (symptoms of SAD via SPS and SIAS) between the two conditions. The software Gpower [86] was used to calculate the sample size of *n* = 100 per group given a Bonferroni-adjusted (due to multiple testing) alpha error level of 0.025 for a one-sided test, a statistical power of 0.80 and an effects size of d = 0.4.

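### Ten imputations are valid, but they leave avoidable random noise in the primary verdict; raising the number to 100 with a recorded seed costs almost nothing

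*Protocol article*

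**What the plan says.** The Analysis section analyses continuous outcomes by ANCOVA, "with pre-scores as a covariate and the post-scores as the dependent variable", under the intention-to-treat principle. On missing values it states "Missing data will be handled using multiple imputations with 10 estimations per missing value", and it cites two missing-data references for this. Tests are one-sided, "at a significance level of 0.025 for the primary outcomes and 0.05 for the secondary outcomes".

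The section on power and sample size uses the same threshold, a "Bonferroni-adjusted (due to multiple testing) alpha error level of 0.025 for a one-sided test", with "a statistical power of 0.80 and an effects size of d = 0.4", and arrives at 100 per group.

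The article gives no expected rate of missing outcomes for this trial. The Background mentions high dropout among possible reasons why effects differed between earlier unguided studies. The Discussion notes that two meta-analyses found lower attrition with support than without. Neither gives a rate. The Procedure section says that the 10-week assessment takes place whether or not the programme was completed.

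**The concern.** Multiple imputation draws random values. With a finite number of imputations, m, the pooled estimate, its standard error and its degrees of freedom all vary from one seed to the next. This variation grows with the FMI and shrinks as m rises.

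The article fixes m = 10, so this is a stated choice and not a detail left open. The primary conclusion rests on whether p falls below 0.025. If a noticeable share of trials would change verdict on a rerun of the same plan with the same data, the confirmatory result carries noise that has nothing to do with the participants and could easily be removed.

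**Working it through.** **Inputs.** From the article: m = 10; d = 0.4; 100 per arm ("The intended sample size of 200 participants will provide sufficient power"; "randomly allocates participants in a 1:1 ratio with a block size of 8"); one-sided alpha 0.025. Complete-data degrees of freedom: 200 − 3 = 197 (intercept, group, baseline score). Assumed, because the article gives no figure: FMI from 0.1 to 0.4, and no precision gained from the baseline covariate unless stated.

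**Step 1: the plan's own figure.** n per arm = 2(1.960 + 0.842)² / 0.4² = 98.1, so 99 by the normal approximation. The exact t-test needs 100 (power 0.804). The stated 100 per group reproduces, and it contains no allowance for missing outcomes.

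**Step 2: efficiency.** Relative efficiency is 1/(1 + FMI/m). With m = 10 it is 0.990, 0.980, 0.971 and 0.962 at FMI 0.1, 0.2, 0.3 and 0.4. Little is lost on average.

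**Step 3: stability of the standard error.** A common rule for a 5% coefficient of variation of the standard error is m = 1 + 0.5(FMI/0.05)².
- FMI 0.1: 1 + 0.5 × 4 = 3
- FMI 0.2: 1 + 0.5 × 16 = 9
- FMI 0.3: 1 + 0.5 × 36 = 19
- FMI 0.4: 1 + 0.5 × 64 = 33

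Ten imputations meet this rule up to an FMI of about 0.2 and fall short from about 0.3.

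**Step 4: a result near the threshold.** The data are held fixed so that unlimited imputations would give z = 2.1, one-sided p about 0.018. In each run the pooled estimate varies around its limit with variance B/m, where B is the between-imputation variance. The estimate of B follows a scaled chi-square with m − 1 degrees of freedom. The total variance is W + (1 + 1/m)B, where W is the within-imputation variance, and small-sample degrees of freedom are used. Share of runs in which the seed alone puts p above 0.025:

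| FMI | m = 10 | m = 50 | m = 100 |
|---|---|---|---|
| 0.1 | 16% | 1% | 0% |
| 0.2 | 29% | 6% | 1% |
| 0.3 | 37% | 13% | 5% |
| 0.4 | 43% | 19% | 10% |

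At FMI 0.3 the 5th to 95th percentile range of p is 0.008 to 0.048 with m = 10, and 0.014 to 0.025 with m = 100.

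**Step 5: averaged over all results expected at the design effect.** Step 4 starts from a borderline result. Here the data vary as well, with d = 0.4 and 100 per arm, and each dataset is imputed twice with different seeds. Probability that the two verdicts on one scale differ:

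| FMI | m = 10 | m = 100 |
|---|---|---|
| 0.1 | 4.0% | 1.2% |
| 0.2 | 7.0% | 2.1% |
| 0.3 | 10.1% | 2.9% |
| 0.4 | 13.1% | 3.7% |

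With an assumed baseline correlation of 0.5, the FMI 0.3 figures are 8.4% and 2.4%. Without the covariate, power at FMI 0.3 rises from about 0.63 with m = 10 to about 0.65 with m = 100.

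**The case against.** The strongest reply is that nothing here is wrong. The (1 + 1/m) term already allows for a finite number of imputations, so tests with m = 10 are valid. Efficiency is at least 96% up to FMI 0.4, and m = 10 meets the standard-error rule up to about 0.2. All of this stands, and it limits the point to reproducibility.

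A reader might infer that the protocol itself expects high attrition and then fixes too few imputations for it. The documents do not support that. Their remarks on dropout concern earlier studies and carry no figures. Leaving the programme is also not the same as a missing 10-week score, because that score is collected regardless of completion. How far m = 10 falls short therefore depends on an assumed FMI.

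The 37% is also easy to over-read. It applies only to a result already close to 0.025. Averaged over the design effect the figure is about 10% at FMI 0.3. If the true effect were the pooled g = 0.78 that the Background reports for unguided programmes, it would be 0.5% or less at that FMI. More imputations do not remove the problem at the threshold itself: with a limiting p of exactly 0.025 and FMI 0.3, p exceeds 0.025 in 57% of runs with m = 10 and in 52% with m = 100.

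Finally, one might ask for imputation by arm with the interim SPS and SIAS scores as auxiliary variables. Those scores are collected only in the intervention arm, and such details commonly belong in an analysis plan that is not shown. They are not part of this point.

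**Conclusion.** The point holds as a minor improvement. At the design effect, going from 10 to 100 imputations cuts seed-driven disagreement to roughly a third: from about 4%, 7%, 10% and 13% to about 1%, 2%, 3% and 4% at FMI 0.1 to 0.4. For a result at p of about 0.018 with FMI 0.3, the cut is from 37% to 5%. These figures concern one primary scale and rest on the assumed FMI, d = 0.4 and, except where stated, no covariate gain. The effect on power is small. The planned inference is valid as it stands.

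**What to change.** In the Analysis section, replace the 10 imputations with 100 (at least 50) and state that the random seed is set in advance and recorded. Fifty would meet the standard-error rule throughout the FMI range of 0.1 to 0.4 used here. One hundred is suggested because the aim is a stable verdict and not only a stable standard error. At FMI 0.3, the near-threshold case still crosses 0.025 in 13% of runs with 50, against 5% with 100.

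The cost is one changed number, one added sentence and minutes of computing. The Economic evaluation section already plans 5000 bootstrap samples, so computing is no constraint.

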**Methods:**

The study is a two arm randomized controlled trial in which 200 university students with a primary diagnosis of SAD will be assigned randomly to either a wait-list control group (WLC) or the intervention group (IG). The intervention consists of 9 sessions of an internet-based cognitive-behavioral treatment, which also includes a module on fear of positive evaluation (FPE). Guidance is delivered only on the basis of standardized automatic messages, consisting of positive reinforcements for session completion, reminders, and motivational messages in response to non-adherence. All participants will additionally have full access to treatment as usual. Diagnostic status will be assessed through Structured Clinical Interviews for DSM Disorders (SCID). Assessments will be completed at baseline, 10 weeks and 6-month follow-up. The primary outcome will be SAD symptoms at post-treatment, assessed via the Social Phobia Scale (SPS) and the Social Interaction Anxiety Scale (SIAS). Secondary outcomes will include diagnostic status, depression, quality of life and fear of positive evaluation. Cost-effectiveness and cost-utility analyses will be evaluated from a societal and health provider perspective.

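### Additional covariates enter the primary ANCOVA only if associated with change in the outcome, so outcome data choose the final model, and by a criterion that does not fit it

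*Protocol article*

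**What the plan says.** The Analysis section of the protocol article specifies an ANCOVA for continuous outcomes, "with pre-scores as a covariate and the post-scores as the dependent variable". The pre-score therefore enters unconditionally.

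The next sentence adds a rule for further covariates: "Possible confounders (e.g. former use of psychotherapy) will be assessed", and these are then "included as covariates if they should be associated with changes in the primary outcome". No model without these additions is named as primary. The variables listed later in the same section serve exploratory moderator analyses and do not settle the covariates of the primary model.

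Two scales carry the primary outcome at post-treatment, SPS and SIAS, each tested one-sided at 0.025. The Randomization section says that the list "randomly allocates participants in a 1:1 ratio with a block size of 8", so any baseline imbalance arises by chance.

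**The concern.** Two features of the stated rule are unsuitable for a confirmatory model.

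- **It depends on the outcome.** Association with change cannot be assessed until post-scores are in, so every covariate beyond the pre-score is decided from the data that the model is meant to test. The two primary scales could end with different covariates.
- **It uses the wrong quantity.** The ANCOVA models the post-score given the pre-score. A covariate helps that model if it predicts the post-score once the pre-score is known. Association with post minus pre is something else: through regression to the mean, any variable correlated with the pre-score tends to correlate with change even if it adds nothing to the ANCOVA.

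At stake are the credibility of a primary estimate whose model was open until the results were known, and the efficiency of the adjustment. Because allocation is randomized, no screening for confounders is needed to make the comparison valid.

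**Working it through.** **Inputs from the protocol article.** N = 200, 100 per arm; one-sided alpha 0.025 per primary scale; power 0.80; d = 0.4; ANCOVA of post-score on arm and pre-score.

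**Assumed, because the article gives no figures.** Pre-post correlation r = 0.6 (range 0.5 to 0.7); correlation c between covariate and pre-score 0.1 to 0.6; a p < 0.05 screen; 5 to 20 candidate covariates.

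**1. The plan's sample size.** n per arm = 2(1.960 + 0.842)² / 0.4² = 98.1, so 99. The exact t-test solution is 99.08, so 100. Power at 100 per arm is 0.80 to 0.81. The stated figure reproduces, and nothing below changes it.

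**2. What the screen measures.** On standardized scores write post = r·pre + b·X + e, with c = corr(X, pre). The coefficient that matters in the ANCOVA is b. The screen instead looks at

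cov(X, post − pre) = b + r·c − c = b − (1 − r)c.

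The two agree only if c = 0 or r = 1.

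**3. Covariates that add nothing (b = 0).** Here var(change) = 2 − 2r, so corr(X, change) = −(1 − r)c / √(2 − 2r). At r = 0.6 this is −0.447c. The selection probability uses Fisher's z with standard error 1/√197:

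| c | corr(X, change) | P(selected), r = 0.6 | P(selected), r = 0.5 to 0.7 |
|---|---|---|---|
| 0.1 | −0.045 | 10% | 11% to 9% |
| 0.2 | −0.089 | 24% | 29% to 19% |
| 0.3 | −0.134 | 47% | 56% to 37% |
| 0.4 | −0.179 | 72% | 81% to 59% |
| 0.6 | −0.268 | 97% | 99% to 91% |

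A screen on the right quantity would pick these covariates 5% of the time.

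**4. Useful covariates that are missed.** If b = (1 − r)c, the covariance with change is exactly zero. At r = 0.6 and c = 0.3, b = 0.4 × 0.3 = 0.12. Over r = 0.5 to 0.7 and c = 0.3 to 0.4, b runs from 0.09 to 0.20. Such a covariate is usually left out although it has a real coefficient in the ANCOVA.

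**5. Cost in precision of wrong selections.** Simulation with five irrelevant covariates at c = 0.4, r = 0.6 and N = 200: the standard error of the treatment effect rises from 0.1133 to 0.1145, and 0.1145 / 0.1133 = 1.011, about 1%. Power at d = 0.4 goes from 0.938 to 0.934.

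**6. Type I error, one-sided nominal 2.5%.** Simulations with N = 200 and r = 0.6:

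- Screen applied mechanically, blind to arm: about 2.5% to 2.7%. In one set of 6,000-replicate runs it reached 2.85%, but there the pre-score-only model gave 2.80%, so the screen itself added nothing visible.
- Most favourable of four options reported (no added covariates, or thresholds 0.05, 0.10, 0.20): 2.8% to 3.2% with 10 to 20 candidates.
- Wider freedom (most favourable of the pre-score-only, all-covariate, screened and each one-covariate-added model): 3.8% to 4.2% with 5 to 20 candidates.

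The last two lines describe an analyst who picks after seeing results. Missing data and multiple imputation were not simulated.

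**The case against.** The best defence is that the rule is nearly harmless. The strongest single predictor, the pre-score, is fixed in advance. A mechanical screen leaves type I error where it was, and an irrelevant covariate costs about 1% in standard error. The one candidate named is former use of psychotherapy, and the article gives no correlation between it and the pre-score; at c = 0.1 the chance of wrong selection is only 10%. Association with change may also be loose wording for association with the outcome given baseline, although the literal reading is the likelier one. All of this stands as a limit on size. It does not remove the defect, because a fuller plan that followed the rule faithfully would still choose covariates from outcome data.

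Four stronger readings are tempting, and the document does not support them:

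- That all covariates are conditional. Only those beyond the pre-score are.
- That the screen is run on change pooled over arms and so absorbs the treatment effect. The article does not say whether it is pooled, within arm or adjusted for arm.
- That the error rate is inflated. This needs someone to report the most favourable of several models, which the article does not authorise.
- That the open list of candidates and the missing threshold are faults in themselves. A condensed article may leave these to a statistical analysis plan that is not shown. The point here is the rule that is stated.

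**Conclusion.** The point holds as a free improvement. The Analysis section states a rule under which outcome data decide the final primary model, and the criterion, b − (1 − r)c, is not the quantity b that the ANCOVA needs. That mismatch is algebra and does not rest on the assumed figures.

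Its size does rest on them. At r = 0.6, N = 200 and a p < 0.05 screen, a covariate with nothing to add is selected about 10% to 72% of the time for c from 0.1 to 0.4. The 97% at c = 0.6 is an extreme case and should not be read as typical. No bias and no material loss of power or error control is shown for the rule applied mechanically. The remaining risk is discretion over the confirmatory model, and the chance that SPS and SIAS are analysed with different covariates.

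**What to change.** Replace the conditional rule with a fixed model for each primary scale: post-score on arm and the baseline score of that scale, plus a short named list of baseline variables, included whatever their observed association with the outcome. Suitable candidates are the baseline score of the other primary scale and former psychotherapy. Use the same list for SPS and SIAS. Keep any data-driven adjustment only as a labelled sensitivity analysis.

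The cost is about a sentence in the Analysis section, settled before outcome data are examined. It needs no new assessments if the named variables are among those already planned, and the sample size stays at 100 per arm.

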### Economic evaluation

We will perform an economic evaluation from the societal and health provider perspectives that include all relevant costs and outcomes. A cost-effectiveness analysis as well as a cost-utility analysis will be conducted following guidelines from the International Society for Pharmacoeconomics and Outcomes Research (ISPOR) Good Research Practices Task Force Report and the recommendations of the Consolidated Health Economic Evaluation Reporting Standard (CHEERS) [92, 93]. In the cost-effectiveness analyses, symptom-free status via SPS and SIAS will be used as clinical outcome. For cost-utility analyses, quality-adjusted life years (QALYs) will be calculated based on the AQOL-8D. EQ-5D-5L will be used only in sensitivity analyses. We will compare both groups in terms of incremental costs and incremental effects, by calculating the incremental cost-effectiveness ratio (ICER). We will use bootstrapping (*N* = 5000) and 95% confidence intervals in percentiles to test the robustness of the ICER and to quantify the uncertainty surrounding the ratios. The results will be shown in a cost-effectiveness plane and in a cost-effective acceptability curve. Additionally, the robustness of the base-case findings will be tested with a multi-way sensitivity analysis (i.e. ± 50% intervention costs, costs outliers, EQ-5D-5L as alternative instrument to calculate QALYs).

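### Symptom-free status, the effect term of the cost-effectiveness analysis, has no stated baseline adjustment; adjusting for baseline SPS and SIAS would make it more precise at almost no cost

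*Protocol article*

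**What the plan says.** The Analysis section of the protocol article treats the two kinds of outcome separately. For continuous outcomes, "Differences in continuous outcomes between the groups will be analyzed using analysis of covariance (ANCOVA), with pre-scores as a covariate". For dichotomous outcomes, "We will also test differences in treatment response rates (50% relative symptom reduction), numbers of participants displaying reliable change", "as well as differences in symptom deterioration rates". It names no model for these, and "Effect sizes between groups of dichotomous outcome variables will be expressed as number needed to treat and its associated 95% confidence intervals".

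One further sentence on covariates follows the ANCOVA sentence: "Possible confounders (e.g. former use of psychotherapy) will be assessed and included as covariates if they should be associated with changes in the primary outcome". It does not name baseline SPS or SIAS, and inclusion is conditional.

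Symptom-free status is not among the rates listed in the Analysis section. It appears in the Economic evaluation section: "In the cost-effectiveness analyses, symptom-free status via SPS and SIAS will be used as clinical outcome". There the groups are compared on incremental costs and effects, with an ICER and 5,000 bootstrap samples. No regression model or covariate is mentioned. Table 2 shows SPS and SIAS measured at baseline in both arms.

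**The concern.** Whether a participant ends below a fixed symptom threshold depends heavily on the starting score. An unadjusted difference in proportions leaves that predictable variation in the error term, and any chance baseline imbalance stays in the estimate. Symptom-free status is the denominator of the ICER in the cost-effectiveness analysis, so avoidable imprecision there carries into the cost-effectiveness plane and the acceptability curve. The plan already adjusts for baseline where the outcome is continuous, and the data needed to do the same here are collected anyway.

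**Working it through.** **The plan's own figure.** With d = 0.4, one-sided alpha 0.025 and power 0.80, the two-sample calculation gives 99 per arm by the normal approximation and 99.08, rounded up to 100, by the t-test. Power at 100 per arm is 0.807. The stated 100 per group reproduces and does not depend on how dichotomous outcomes are analysed.

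**Method.** Let Y be the binary outcome, X the baseline score and p_a(X) the logistic prediction in arm a.

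- Raw risk difference with n per arm: variance = [P0(1−P0) + P1(1−P1)]/n.
- Standardised risk difference: variance ≈ [E(Y−p0(X))² + E(Y−p1(X))²]/n, plus a small term Var(p1(X)−p0(X))/(2n).
- Variance ratio VR = adjusted/raw. Effective sample-size gain = 1/VR − 1.

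**Inputs.** From the article: 100 per arm, d = 0.4, and one-sided 0.05 for secondary outcomes. Everything else is assumed, because the article gives no correlations, SDs, thresholds or rates.

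**Calculation 1.** 3,000 simulated trials per cell, with rates of about 20–31% against 33–46% and influence-function standard errors.

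| Outcome | r = 0.5 | r = 0.6 | r = 0.7 |
|---|---|---|---|
| Symptom-free, VR | 0.86 | 0.79–0.80 | 0.68–0.70 |
| Reliable change, VR | 0.86 | 0.91 | 0.92 |
| 50% response, VR | 1.01 | 1.00 | 0.98 |

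For symptom-free status the variance falls by 1 − 0.86 = 14% up to 1 − 0.68 = 32%. Null runs rejected at 0.09–0.11 (nominal 0.10) with and without adjustment.

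**Calculation 2.** Different assumptions: baseline mean 50, SD 12; control post-score mean 46, SD 14; symptom-free threshold 33; reliability 0.92.

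| Outcome | r = 0.4 | r = 0.6 | r = 0.75 |
|---|---|---|---|
| Symptom-free, VR (gain) | 0.912 (10%) | 0.790 (27%) | 0.649 (54%) |
| Reliable change, VR (gain) | 0.873 (15%) | 0.942 (6%) | 0.984 (2%) |
| Deterioration, VR (gain) | 0.910 (10%) | 0.965 (4%) | 0.994 (1%) |
| 50% response, VR (gain) | 1.000 (0%) | 0.988 (1%) | 0.942 (6%) |

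These ratios omit the small last term. Adding it for symptom-free status moves the ratio by no more than about 0.01.

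Worked example for symptom-free status at r = 0.6: P0 = 0.175 and P1 = 0.298, so the difference is 0.123. The raw standard error is √[(0.175×0.825 + 0.298×0.702)/100] = 0.0595. Power at one-sided 0.05 is Φ(0.123/0.0595 − 1.645) = 0.66. The adjusted standard error is 0.0595 × √0.790 = 0.0529, and power becomes Φ(0.123/0.0529 − 1.645) = 0.75.

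The two calculations agree where they overlap: about 20–21% less variance at r = 0.6.

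**Effect of the entry cut-offs.** Participants must exceed a cut-off on SPS or SIAS. If that truncates the baseline distribution, baseline explains less of the outcome. With truncation assumed, the variance reduction for symptom-free status falls to about 4–24%, depending on the correlation and on how much of the distribution is cut off. Because exceeding the cut-off on either scale is enough, truncation on each single scale would be partial.

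**The case against.** The strongest case against is that the article never says the comparison is unadjusted. A number needed to treat, or an incremental effect, can be derived from an adjusted risk difference, and an article may leave the model to a fuller document that is not shown. This stands in part: no adjusted model is ruled out. But the article does specify baseline adjustment for one class of outcome and describes the other separately without it, so unadjusted is the natural reading. The point also proposes a better method rather than asking for missing detail.

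Second, the change-based outcomes already contain the baseline in their definition, and the gain for them is small. This stands, and it is why the point rests on symptom-free status.

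Third, the size depends on assumptions. This also stands. The correlation is unknown, and the entry cut-offs would tend to reduce the gain. The power figures matter less than the variance figures, because the Economic evaluation section plans an ICER with bootstrap uncertainty, and symptom-free status is not in the list of tested rates.

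Fourth, a logistic model yields a conditional odds ratio rather than the planned marginal measure. Standardisation answers this: it returns a marginal risk difference, whose inverse is the NNT.

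A reader might infer that all the dichotomous results are seriously imprecise or biased, or that the article states raw-rate comparisons outright. The documents support neither. Randomisation makes the unadjusted comparison valid, and the figures show a sizeable gain for one outcome only.

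**Conclusion.** The point holds as a free improvement confined mainly to symptom-free status in the cost-effectiveness analysis. Under assumed pre-post correlations of 0.5–0.7, baseline standardisation cuts the variance of the between-group difference by about 14–32%. If the entry cut-offs restrict the baseline range, the figure is about 4–24% over a wider range of assumptions. For reliable change and deterioration the variance reduction is about 1–14%. No gain is claimed for 50% response, where it is close to nil, or for SCID diagnostic status, for which nothing was computed. Nothing in the plan is invalid as written: the estimand and type I error do not change, and the primary ANCOVA and the sample size of 100 per group stand.

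**What to change.** In the Economic evaluation section, state that the incremental effect on symptom-free status will be estimated from a logistic model containing arm and baseline SPS and SIAS, standardised over the whole randomised sample to a marginal risk difference, and refitted within each bootstrap sample and each imputed data set. Keep raw counts and rates as description.

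Optionally, in the Analysis section, use the same model for reliable change and deterioration, with the NNT and its interval taken from the standardised risk difference. The reason there is consistency more than precision.

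The cost is a few sentences of wording and one short model per outcome. With 10 imputations and 5,000 bootstrap samples, fully crossed, that is 10 × 5,000 = 50,000 quick fits. No new data are needed, and the target of estimation is unchanged.

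### Two unreconciled sidedness rules leave secondary tests out of step with their 95% intervals and the deterioration test without a stated direction

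*Protocol article*

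**What the plan says.** All the statements are in the protocol article.

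- **Analysis, main paragraph, last sentence:** every reported p-value is "one-sided) at a significance level of 0.025 for the primary outcomes and 0.05 for the secondary outcomes".
- **Analysis, moderator paragraph, last sentence:** "All directional hypotheses are tested one-sided, bidirectional hypotheses two sided". The article does not list which hypotheses belong to which class.
- **Analysis, intervals:** standardised effect sizes are reported "including the 95% confidence intervals for all effect sizes". Between-group effects on dichotomous outcomes are "expressed as number needed to treat and its associated 95% confidence intervals".
- **Analysis, deterioration:** the trial will test response rates and reliable change "as well as differences in symptom deterioration rates". No direction is given for this comparison.
- **Power and sample size calculation:** 100 per group, from a Bonferroni-adjusted "alpha error level of 0.025 for a one-sided test, a statistical power of 0.80 and an effects size of d = 0.4".
- **Study design:** the trial is framed as a test of the intervention's assumed superiority over the wait-list control.

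**The concern.** Three things follow from these sentences.

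First, the two sidedness rules cannot both be applied as written. One makes every p-value one-sided; the other makes some two-sided. With no list of directional hypotheses, the choice for a given outcome could be made after the data are seen.

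Second, a one-sided test at 0.05 corresponds to a 90% interval, not a 95% one. A secondary outcome can therefore be called significant next to an interval that includes no effect, and the reader has no rule for which to believe.

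Third, deterioration is the comparison in which a difference against the intervention matters most. The only direction the article supplies is superiority. A one-sided test pointed that way treats more deterioration in the intervention group as mere absence of benefit.

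**Working it through.** **Inputs.** 100 per arm, d = 0.4, power 0.80 and one-sided alpha 0.025 come from the power section. One-sided 0.05 for secondary outcomes and 95% intervals come from Analysis. The intervals are taken as conventional two-sided ones, which the article does not say explicitly. Deterioration rates are not given and are assumed below.

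**1. The plan's own figure.** n per arm = 2(z₀.₉₇₅ + z₀.₈₀)²/d² = 2(1.960 + 0.842)²/0.16 = 98.1, so 99. The t-test version gives 99.08, so 100. Power at 100 per arm is 0.804. The stated sample size reproduces.

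**2. Primary outcomes: test against interval.** One-sided 0.025 uses z = 1.960, the same multiplier as a two-sided 95% interval. Test and interval agree.

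**3. Secondary outcomes: test against interval.** SE(d) ≈ √(2/100) = 0.1414.

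- Smallest d significant at one-sided 0.05: 1.645 × 0.1414 = 0.233.
- Smallest d whose 95% interval excludes zero: 1.960 × 0.1414 = 0.277.
- Between these values the two disagree. For d = 0.25: z = 0.25/0.1414 = 1.768, one-sided p = 0.039, interval 0.25 ± 0.277 = -0.03 to 0.53.

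The chance of landing in that band is P(1.645 < Z < 1.960), with Z normal, mean d√50 and variance 1:

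| True d | Probability of disagreement |
|---|---|
| 0.20 | 0.116 |
| 0.25 | 0.125 |
| 0.30 | 0.119 |

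That is about 12% per outcome for true effects of this size.

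**4. Deterioration.** Assume observed rates of 15% (intervention) and 5% (control), 100 per arm. Pooled rate 0.10; z = 0.10/√(2 × 0.10 × 0.90/100) = 0.10/0.0424 = 2.357. Two-sided p = 0.018. One-sided p towards benefit = 0.991.

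Power to detect the excess over a range of assumed true rates, at 0.05:

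| Control vs intervention | Two-sided | One-sided towards benefit | One-sided towards harm |
|---|---|---|---|
| 5% vs 15% | 66% | under 0.01% | 76% |
| 5% vs 20% | 90% | under 0.01% | 95% |
| 10% vs 20% | 51% | about 0.01% | 63% |

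The entries in the benefit column are the chance of wrongly declaring less deterioration; that test has no rejection region for harm.

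**5. What the interval would show.** For 15% versus 5%, the risk difference is 0.10 with SE √(0.15 × 0.85/100 + 0.05 × 0.95/100) = 0.0418, so the 95% interval is 1.8 to 18.2 percentage points. On the planned scale that is a number needed to harm of 10, with limits 1/0.182 = 5.5 and 1/0.018 ≈ 56. The excess would be visible there whatever the direction of the p-value.

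**The case against.** The best defence is that the second rule closes the moderator paragraph and may govern moderator analyses only; then the main rule would stand for everything else. That reading is possible, but the text does not say so. Both sentences are worded for all cases, and the first would still cover any moderator p-value that is reported.

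A second defence is that the deterioration test is not said to point towards benefit. This stands. Under the moderator paragraph's rule it could be two-sided, and a one-sided test aimed at harm would have more power than a two-sided one. A reader might infer that the trial cannot show harm at all. The documents do not support that: the direction is unstated, and the planned 95% interval could display an excess. What remains is that the comparison depends on a direction nobody has written down.

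Third, no decision rule uses the intervals, so the secondary mismatch is an inconsistency of reporting and not a formal contradiction. That is fair, but it still leaves a more lenient threshold than the interval beside it implies.

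A reader might also carry the criticism over to the primary outcomes: that the interval mismatch applies there, that going one-sided cancels the Bonferroni step, or that power should be restated as 0.715. None of these follows. One-sided 0.025 per scale agrees with a two-sided 95% interval. Bonferroni over two scales controls the one-sided family level of 2 × 0.025 = 0.05, and the per-scale level and its one-sidedness are openly stated. The figure 0.715 is the power of an unadjusted t-test at one-sided 0.0125 per scale, a stricter standard that the plan did not adopt, and the planned analysis is an ANCOVA on the pre-score. Preferring that standard is a legitimate view, not an error in the document.

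**Conclusion.** The point holds for secondary outcomes and for the deterioration comparison, and not for the primary analysis.

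- The two sidedness rules conflict as written.
- For secondary outcomes, test and interval disagree for observed d of about 0.233 to 0.277. This rests on 100 per arm, no covariate adjustment, no missing data, a normal approximation and two-sided intervals; adjustment or dropout would move the band but not remove it.
- The harm point is conditional. It applies if the deterioration test is one-sided towards benefit, which the superiority framing suggests but the article does not state. The 15% and 5% rates are illustrative.
- The primary tests are consistent with their intervals, and the sample size is arithmetically correct.

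**What to change.** Replace the two sentences in Analysis with a single sidedness rule:

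- Secondary outcomes: two-sided tests at 0.05, matching the 95% intervals.
- Symptom deterioration: an explicitly two-sided test.
- Primary outcomes: one-sided 0.025 for each of SPS and SIAS may stay, with a statement that this gives a one-sided family-wise level of 0.05.
- Moderator analyses: name their sidedness in the same rule, so that no second rule is needed.

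This should be settled before unblinded data are analysed, since a choice of sidedness made afterwards would not be credible.

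The cost is wording. No participants or data are added, and 100 per arm and the stated power of 0.80 are unchanged. The downside is that the smallest significant secondary effect rises from about d = 0.233 to 0.277 on the approximation above, so some borderline secondary results would no longer be called significant.
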